#### Randomization

2.3.3

Patients will be randomized in a 1:1 ratio using block randomization to rosuvastatin and NACTRT or NACTRT alone. An independent statistician will generate the randomization code and independent research staff will inform the study team of the allocation. A randomization log will be maintained by the study team.

#### Treatment

2.3.4

##### Standard of care

2.3.4.1

Both the study groups will receive NACTRT as per the standard of care. Furthermore, 45–50 Gy of radiotherapy will be administered to the pelvis for period of 5–6 weeks. Concurrent tablets of capecitabine of 825mg/m2 will be administered orally twice daily from day 1 to day 35 along with radiotherapy.

##### Study intervention

2.3.4.2

Patients in the study arm will receive 20 mg rosuvastatin orally once daily along with NACTRT for 6 weeks followed by rosuvastatin alone for another 6–10 weeks until surgery (12–16 weeks of statin therapy until surgery or confirmation of ineligibility for surgery). Patients in the control arm will receive only NACTRT as described above, which is the standard of care (**Figure 2**).

**Figure 2 f2:**
[figure not shown]
CONSORT flow diagram depicting the trial schema for treatment decisions. .

##### Drug dispensing

2.3.4.3

Rosuvastatin will be dispensed at randomization and at week 7. Patients who have logistical issues will be dispensed 16 weeks of rosuvastatin prior to starting NACTRT. Patients will be asked to provide used and unused packs of the drug at each visit and a pill count will be conducted and details noted in the case record form (CRF) and drug dispensing logs.

#### Follow-up procedures

2.3.5

After commencing the statin, the patients in the intervention arm will be reviewed every 2 weeks on NACRT (at 2 weeks ± 3 days, 4 weeks ± 3 days, and 6 weeks ± 3 days) either in person in the clinic or telephonically if they cannot come to the clinic due to unavoidable circumstances. Patients in the standard arm on NACTRT will be reviewed as per standard protocol. Patients in both arms will be reviewed at 6 ± 2 weeks after completion of NACTRT (weeks 12–14). At this visit, all patients will undergo restaging as per routine practice and will be evaluated by the MDTB for surgery by week 14 (± 2 weeks). Patients in both arms will be operated on if deemed to have operable disease.

#### Assessment of response

2.3.6

Clinical and radiological assessment will be done at 6–8 weeks after completion of NACTRT. Eligible patients will undergo standard surgery (anterior resection, abdominoperineal resection, inter-sphincteric resection, or multi-visceral resection) according to the level and extent of growth. If the reassessment MRI at 12–14 weeks after completion of NACTRT shows inoperable disease, then the patient will be deemed a non-responder and analyzed as part of the non-pCR group. These patients, if on the rosuvastatin arm, will stop the statin on the day they are deemed inoperable by the MDTB. These patients will receive further chemotherapy to downstage the disease as per the current standard of care. A histopathological examination will be conducted for the patients operated on and the pathological response rate and tumor regression grade (TRG) will be judged according to the American Joint Committee on Cancer (AJCC) (**Appendix 1** in **Supplementary Material**). A pCR is defined as no residual cancer found on histological examination of the TME specimen (Grade 0 AJCC or Grade 1 Mandard’s). The pathologist assessing the specimen will be blinded to the treatment that the patient received.

Following surgery and the availability of the histopathology report, the patient would have completed the active phase of the study and will be followed up according to standard follow-up protocol. Survival details will be collected at each follow-up visit or telephonically if the patient misses a visit for any reason.

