### Study design

2.1

The study is a prospective, randomized, open-label phase II/III study.

For the phase II part of the study, eligible patients will be randomized 1:1 to the statin + NACTRT arm or the only NACTRT (standard) arm. The statin arm will receive rosuvastatin 20 mg for 12–16 weeks. Pathological response would be assessed following surgery.

A follow-on phase III trial with 3-year DFS as the endpoint will be planned depending on how the statin arm fares in terms of feasibility, safety, and efficacy.

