#### End of study visit

2.3.7

Patients will receive rosuvastatin for 12–16 weeks, with the treatment being discontinued 1 day prior to surgery for operable patients. The final study visit for these patients will coincide with their MDTB appointment, where the final surgical histopathology report (approximately 10–14 days post-surgery) will be reviewed. For patients deemed inoperable, the study will conclude on the day the decision of inoperability is made. At this visit, a final safety follow-up and pill count will be conducted. Following this, there will be no further active intervention, and patients will be monitored for survival. No protocol-mandated imaging or re-evaluation is planned; patients will be followed according to standard surveillance guidelines for rectal cancer patients who have undergone multimodality treatment.

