#### Study specific investigations

2.3.8

All investigations will be done as per the current standard of care. There will be no additional planned blood tests or imaging done for the purpose of the study. In patients who agree to participate in the molecular sub-study, the baseline samples will be taken at the time of the baseline endoscopy and post-treatment samples for the operated patients will be from the resected specimen. Post-treatment samples for patients who are not operated on (approximately 30% of those receiving NACTRT) will be collected by conducting a repeat limited sigmoidoscopy. The patients will be reimbursed for this and the same is mentioned in the ICF as well. The follow-up will be as per the prevailing standard of care.

The schedule of events are depicted in **Table 3**.

**Table 3 T4:** Schedule of events.

	Baseline	Randomization	Week 2 visit ±3 days	Week 4 visit ± 3days	Week 6 and 7 visit ±3 days	Week 12 visit ±3 Days	Week 14 to 16 visit ±3 days
Informed Consent	✓						
Screening of patients with biopsy-confirmed adenocarcinoma of the rectum	✓						
Collection of four additional tissue samples for molecular sub-study	✓						
Collection of 7–8 ml of blood	✓						
Randomization		✓					
Both arms NACTRT			✓	✓	✓		
Statin dispensed		✓			✓		**
Statin pill counts			✓	✓	✓		✓
Adverse event/serious adverse event reporting			✓	✓	✓	✓	✓
Clinical review			✓	✓	✓	✓	✓
Radiological review						✓*	✓*
MDTB decision for surgery							✓
Collection of four additional tissue sample post-surgery							✓#

*Radiological assessment will be done at 6–8 weeks after completion of NACTRT.

**Rosuvastatin will be stopped a day prior to surgery (operable patients) or on the day deemed inoperable (inoperable patients).

#Paired tissue samples will be collected from patients who are operated on via the resected specimen (post-treatment sample) or fresh biopsies for patients who are not operated on.

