#### Withdrawal/stopping criteria

2.3.9

The patient will be withdrawn from the study if:

The patient develops unacceptable toxicity.If the patient wishes to withdraw from participation.There is a need for a dose reduction of more than 1 level or discontinuation of the study drug.The patient does not comply with the protocol.

Patients who are not operated on despite a response will not be analyzed in the phase II study but will be followed up for survival and included in the analysis of the phase III study if it is conducted.

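### Only the pathologist is described as blinded; no masking is described for the restaging MRI read and tumour-board decision that determine who is counted as non-pCR without histology or leaves the phase II analysis

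*Protocol article*

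**What the plan says.** All references are to the protocol article.

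- **Masking.** Section 2.1 (Study design): "The study is a prospective, randomized, open-label phase II/III study". Section 2.3.4.2 gives controls NACTRT only, with no placebo. Section 2.3.6 (Assessment of response) names the one blinded role: "The pathologist assessing the specimen will be blinded to the treatment that the patient received".
- **The decision step.** Section 2.3.5 (Follow-up procedures): "all patients will undergo restaging as per routine practice and will be evaluated by the MDTB for surgery". No masking of the MRI reader or the board is described.
- **Route 1, non-pCR without histology.** Section 2.3.6 says that if the reassessment MRI "shows inoperable disease, then the patient will be deemed a non-responder and analyzed as part of the non-pCR group". Such patients on rosuvastatin "will stop the statin on the day they are deemed inoperable by the MDTB". Section 2.3.7 (End of study visit) adds, for the visit that closes the study: "At this visit, a final safety follow-up and pill count will be conducted".
- **Route 2, removal from the analysis.** Section 2.3.9 (Withdrawal/stopping criteria): "Patients who are not operated on despite a response will not be analyzed in the phase II study".
- **Endpoint definition.** Section 2.5 defines pCR on resected specimens from patients who have surgery.
- **Size of the unoperated group.** Section 2.3.8 refers to "Post-treatment samples for patients who are not operated on (approximately 30% of those receiving NACTRT". Section 2.4 gives about 70% undergoing surgery and 15–20% developing progressive disease.

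**The concern.** A blinded pathologist protects the reading of a specimen, but not the decision about who has one. In this trial that earlier decision has direct consequences for the primary endpoint. A patient called inoperable enters the denominator as a failure. A responder who is not resected leaves the denominator altogether.

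Both calls involve judgement at the margin, and the design gives no assurance that they are made without knowledge of the arm. If expectations about the statin influenced them, the arms would differ in who is counted, and blinded histology could not undo that. At stake is the phase II pCR comparison, on which the decision to go on to phase III depends.

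**Working it through.** **Inputs.** From section 2.4: pCR 15% (control) and 25% (statin), two-sided alpha 0.10, 288 evaluable (144 per arm at 1:1), 316 randomised, about 70% operated, 15–20% with progressive disease. From section 2.3.8: about 30% not operated on. The shifts in steps 2 to 4 are assumptions, not document figures.

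**Step 1. How many patients are exposed.** The plan's two figures agree: 100% − 70% = 30% unoperated.
- All unoperated: 0.30 × 316 = 94.8, about 95.
- If all patients with progressive disease are among them, the remainder is 30% − 20% = 10% to 30% − 15% = 15%.
- Discretionary pool: 0.10 × 316 = 31.6 to 0.15 × 316 = 47.4, about 32–47 patients. Per 144-patient arm that is about 14–22.

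The protocol does not say how progressive disease and non-operation overlap. The range is therefore 32–47 with full overlap, and up to 95 with none.

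**Step 2. Route 1, borderline-inoperable patients.** Suppose the board handles 5% of one arm differently (0.05 × 144 = 7.2, about 7), each with a 5–15% chance of pCR if resected.
- Events moved: 7 × 0.05 = 0.35 to 7 × 0.15 = 1.05.
- Shift in the rate: 0.35/144 = 0.2 points to 1.05/144 = 0.7 points.

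**Step 3. Route 2, responders not operated on.** Suppose the same 7 patients are good responders with a 50% chance of pCR, and they leave the analysis under section 2.3.9.
- Expected pCRs at 15%: 0.15 × 144 = 21.6.
- After removal: (21.6 − 7 × 0.5)/(144 − 7) = 18.1/137 = 13.2%, a shift of 1.8 points.

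The change of denominator to 137 comes entirely from the section 2.3.9 exclusion. Seven patients is a third to a half of the 14–22 in step 1, so this is a sizeable imbalance rather than a typical one.

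**Step 4. Effect on the test.** With no true effect, each tail of a two-sided 0.10 test is 5%. The tail favouring the statin is 1 − Φ((1.645 × se0 − d)/se1). Here d is the biased difference, se0 the pooled and se1 the unpooled standard error.

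| Assumed bias toward the statin | n (control / statin) | se0 | se1 | Tail |
|---|---|---|---|---|
| 0 | 144 / 144 | 0.0421 | 0.0421 | 5.0% |
| 0.2 points (route 1, low) | 144 / 144 | 0.0422 | 0.0422 | 5.6% |
| 0.7 points (route 1, high) | 144 / 144 | 0.0425 | 0.0425 | 7.0% |
| 1.8 points (route 2, loss in control arm) | 137 / 144 | 0.0416 | 0.0415 | 11.2% |

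The direction can reverse. If the seven responders are lost from the statin arm instead, and its true rate is 25%, the observed rate is (0.25 × 144 − 3.5)/137 = 32.5/137 = 23.7%. Power at two-sided 0.10 falls from 68% to 58%. The 68% is the power of 144 per arm at the stated two-sided alpha; that it falls short of the stated 80% is a separate matter.

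**The case against.** **Nothing says the reader or the board is told the arm.** This is correct. A reader might infer that the MRI is read and the board decides with the allocation known, but no section says so. The pill count and the statin stop show that the arm is visible around the inoperability decision. They do not show what the radiologist knew when reading the scan. The supportable statement is that masking of these steps is not described, in an open-label trial whose text does specify masking for the pathologist.

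**About a third of patients is too many.** This largely stands. It is tempting to treat all of the roughly 95 unoperated patients as open to judgement. Progressive disease probably accounts for half to two-thirds of them, and much of it is likely to be clear-cut. Others may be unoperated through refusal or withdrawal.

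**Coding inoperable disease as non-pCR is nearly outcome-neutral.** This also stands. Under the assumed 5–15% chance of pCR, misjudging such patients moves the rate by less than 1 point, against a planned difference of 10.

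**The larger effect comes from the exclusion rule, and its direction may be conservative.** Both parts are fair. The 13.2% figure depends on section 2.3.9, and sparing more statin-arm responders from surgery would work against the statin. But the exclusion matters for masking because the board's decision triggers it, and a bias of unknown direction is not thereby harmless.

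**The endpoint is histological and read blind.** This is true of the reading. A reader might go further and conclude that the endpoint as a whole is unprotected, and the text does not support that. The gap concerns who is resected, counted or excluded.

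**Conclusion.** The point holds as a limited weakness in the design. Masking is specified for the specimen reading, but none is described for the restaging MRI and board decisions that select patients into the endpoint.

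The probable exposure is about 32–47 of 316 patients, assuming that those with progressive disease fall within the unoperated 30%. The inoperable route is worth less than 1 point. The exclusion of unoperated responders matters more: about 1.8 points in the illustration, in either direction, which takes a 5% false-positive tail to about 11% or power from 68% to 58%. These effects require a difference between arms in board decisions that the documents neither show nor rule out. The point justifies an inexpensive safeguard; it does not show that the primary result will be biased.

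**What to change.** 1. The radiologist who already reads the restaging MRI reads it without the allocation on the request. Section 2.3.6 places the assessment at 6–8 weeks and the reassessment MRI at 12–14 weeks after NACTRT; these must be reconciled so that it is clear which scan is meant.
2. The board records one of three categories (operable, inoperable, responder not for resection), with the reason, before the allocation is disclosed for any instruction about the study drug.
3. Unoperated patients are reported by arm and reason.
4. Sections 2.3.6, 2.3.9 and 2.5 are reconciled to one analysis rule covering every unoperated randomised patient. Masking alone is not enough: if the statin produced more good responders, a fully masked board could still leave more of them unoperated, and so excluded, in that arm.

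The cost is a masked request form, one board form and a clarified analysis rule, with no extra reader, scan or visit. Masking will be incomplete, because clinicians on the board may already know the arm. Section 4 reports monitoring already carried out, so the trial is under way, and patients already assessed cannot be masked retrospectively. For them, the third and fourth changes still apply.

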#### End of study visit

2.3.7

Patients will receive rosuvastatin for 12–16 weeks, with the treatment being discontinued 1 day prior to surgery for operable patients. The final study visit for these patients will coincide with their MDTB appointment, where the final surgical histopathology report (approximately 10–14 days post-surgery) will be reviewed. For patients deemed inoperable, the study will conclude on the day the decision of inoperability is made. At this visit, a final safety follow-up and pill count will be conducted. Following this, there will be no further active intervention, and patients will be monitored for survival. No protocol-mandated imaging or re-evaluation is planned; patients will be followed according to standard surveillance guidelines for rectal cancer patients who have undergone multimodality treatment.

#### Study specific investigations

2.3.8

All investigations will be done as per the current standard of care. There will be no additional planned blood tests or imaging done for the purpose of the study. In patients who agree to participate in the molecular sub-study, the baseline samples will be taken at the time of the baseline endoscopy and post-treatment samples for the operated patients will be from the resected specimen. Post-treatment samples for patients who are not operated on (approximately 30% of those receiving NACTRT) will be collected by conducting a repeat limited sigmoidoscopy. The patients will be reimbursed for this and the same is mentioned in the ICF as well. The follow-up will be as per the prevailing standard of care.

The schedule of events are depicted in **Table 3**.

**Table 3 T4:** Schedule of events.

	Baseline	Randomization	Week 2 visit ±3 days	Week 4 visit ± 3days	Week 6 and 7 visit ±3 days	Week 12 visit ±3 Days	Week 14 to 16 visit ±3 days
Informed Consent	✓						
Screening of patients with biopsy-confirmed adenocarcinoma of the rectum	✓						
Collection of four additional tissue samples for molecular sub-study	✓						
Collection of 7–8 ml of blood	✓						
Randomization		✓					
Both arms NACTRT			✓	✓	✓		
Statin dispensed		✓			✓		**
Statin pill counts			✓	✓	✓		✓
Adverse event/serious adverse event reporting			✓	✓	✓	✓	✓
Clinical review			✓	✓	✓	✓	✓
Radiological review						✓*	✓*
MDTB decision for surgery							✓
Collection of four additional tissue sample post-surgery							✓#

*Radiological assessment will be done at 6–8 weeks after completion of NACTRT.

**Rosuvastatin will be stopped a day prior to surgery (operable patients) or on the day deemed inoperable (inoperable patients).

#Paired tissue samples will be collected from patients who are operated on via the resected specimen (post-treatment sample) or fresh biopsies for patients who are not operated on.

#### Withdrawal/stopping criteria

2.3.9

The patient will be withdrawn from the study if:

The patient develops unacceptable toxicity.If the patient wishes to withdraw from participation.There is a need for a dose reduction of more than 1 level or discontinuation of the study drug.The patient does not comply with the protocol.

Patients who are not operated on despite a response will not be analyzed in the phase II study but will be followed up for survival and included in the analysis of the phase III study if it is conducted.

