**Methods:**

This is a prospective, randomized, open-label phase II/III study. The phase II study has a sample size of 316 patients (158 in each arm) to be accrued over 3 years to have 288 evaluable patients. The standard arm will receive NACTRT while the intervention group will receive 20 mg rosuvastatin orally once daily along with NACTRT for 6 weeks followed by rosuvastatin alone for 6–10 weeks until surgery. All patients will be reviewed after repeat imaging by a multidisciplinary tumor board at 12–16 weeks after starting NACTRT and operable patients will be planned for surgery. The pathological response rate, tumor regression grade (TRG), and post-surgical complications will be recorded.

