### Sample size and duration of the study

2.4

Each year, approximately 180–200 rectal cancer patients receive NACTRT at our hospital, with approximately 70% undergoing surgery and 15%–20% developing progressive disease. The current pCR rate at our hospital following NACTRT is approximately 15%, while the literature indicates a pCR rate of 25%–30% with statin therapy. We hypothesize that rosuvastatin can increase the pCR rate by 10%, from 15% to 25%. To detect a 10% difference in pCR rates, with a two-sided alpha of 0.10 and 80% power, a sample size of 288 patients would be required. Factoring in a 10% attrition rate, the total sample size increases to 316. Approximately 500–600 patients will need to be screened to enroll 316 participants. It is estimated that accrual and analysis will take approximately 3 years to complete.

A follow-on phase III trial is also will be planned depending on the success of the phase II study, which will compare the 3-year DFS in the two arms. All the patients in the phase II study will be included in the survival statistics in the follow-on phase III study which will be statistically powered for survival. Assuming that the addition of rosuvastatin to NACTRT will improve the 3-year DFS from 60% to 67%, our calculated sample size will be 1,135 subjects (567 in the control group and 568 in the treatment group) (a two-sided log-rank test with 80.0% power at a 0.050 significance level). This assumes a uniform accrual pattern across time periods and 10% dropout rate. If we move on to the phase III study, another 4 years will be required for accrual. The total duration will be 7 years for accrual and 3 years for follow up.

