## Limitations

5

If any adverse effects of rosuvastatin are reported, they will be managed according to the National Lipid Association (NLA) Statin Safety Task Force guidelines (40, 41). According to these, monitoring CK levels is recommended only for symptomatic patients. The first-level dose reduction will be to 10 mg. If another level of reduction is required, the drug will be discontinued and the patient will be withdrawn from the study. Moreover, there are studies that have reported the effect of alcohol consumption, smoking, and body mass index on treatment response to statins (47, 48). However, the status of these was not considered in our exclusion criteria for the study. Further, the proposed study protocol has a short follow-up duration for phase II which could be improved if the study is extended for phase III.

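### Stopping or substantially reducing rosuvastatin takes the patient out of the study, a trigger only one arm can meet, so drug discontinuation should be separated from study withdrawal

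*Protocol article*

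**What the plan says.** Section 2.3.9 gives four reasons for withdrawing a patient from the study: unacceptable toxicity, the patient's own wish, a study-drug trigger and non-compliance. The study-drug trigger reads "There is a need for a dose reduction of more than 1 level or discontinuation of the study drug". The non-compliance trigger reads "The patient does not comply with the protocol". Section 5 (Limitations) repeats the drug rule and names the two steps separately: if a further dose level is needed, "the drug will be discontinued and the patient will be withdrawn from the study".

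Allocation is 1:1 (section 2.1), and controls receive chemoradiation without a study drug (section 2.3.4.2). Pill counts (section 2.3.4.3), weekly calls to confirm intake (section 3.2) and two-weekly reviews during chemoradiation (section 2.3.5) concern the rosuvastatin arm. Section 2.3.5 leaves controls to routine review.

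On numbers, section 2.4 states "Factoring in a 10% attrition rate, the total sample size increases to 316", and the abstract describes the 316 as "to be accrued over 3 years to have 288 evaluable patients". Section 2.4 also says that every phase II patient will enter the survival analysis of a follow-on phase III trial. Section 2.3.10 requires adverse events to be followed until they resolve or stabilise.

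**The concern.** Stopping a drug and leaving a trial are different events, and the rule merges them. Whether a patient meets the study-drug trigger depends on the assigned arm and on what happens after randomisation. If such patients are then missing from the pCR comparison, the arms compared are no longer the arms randomised. Patients who cannot tolerate the statin may also be those less likely to respond. Removing them from one arm would then raise that arm's observed pCR rate without any drug effect.

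The pCR result bears on whether phase III goes ahead (sections 1.3 and 2.1). A later analysis plan can define an as-randomised population, but it cannot recover pathology or follow-up that was never collected because the patient had been taken out of the study.

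**Working it through.** **1. What the text settles**

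| Question | Text | Reading |
|---|---|---|
| Does stopping the drug mean leaving the study? | 2.3.9 and 5 | Yes, stated twice |
| Can a control meet the study-drug trigger? | 2.3.4.2 | No, controls have no study drug |
| Can a control be withdrawn for toxicity, own wish or non-compliance? | 2.3.9 | Yes, none of these names an arm |
| Is non-compliance equally detectable in both arms? | 2.3.4.3, 2.3.5, 3.2 | No, adherence checks concern the statin |
| Is pathology or survival collected after withdrawal? | 2.3.9, 5 | Not stated |
| Are withdrawn patients left out of the pCR analysis? | Abstract, 2.4 | Suggested by the evaluable target and the attrition allowance, not stated |
| Is there a pCR rule that could cover them? | 2.3.6 | Inoperable patients count as non-pCR; withdrawn patients are not mentioned |

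**2. The plan's own figures**

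Attrition: 288 × 1.10 = 316.8, which matches the stated 316; 288 / 0.90 = 320. The plan therefore allows for about 28 non-evaluable patients (316 − 288), without saying in which arm or for what reason.

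The 288 itself is stated as "with a two-sided alpha of 0.10 and 80% power, a sample size of 288 patients would be required". With pCR 15% against 25% and the pooled normal approximation, two-sided 0.10 gives 197 per arm (394). One-sided 0.10 gives 144 per arm (288). That mismatch is a separate matter and this point does not depend on it.

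**3. Size of a possible bias**

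From the documents: 158 per arm, pCR 15%, two-sided 0.10 (5% in the tail favouring the statin). Assumed, because the documents do not give them: true pCR 15% in both arms; a share w of the statin arm withdrawn and dropped; pCR of p_w among those withdrawn; no controls dropped.

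Observed statin pCR = (0.15 − w·p_w) / (1 − w).

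Example, w = 10% and p_w = 5%:
- Observed rate: (0.15 − 0.005) / 0.90 = 0.1611, a bias of +1.1 points.
- Patients left in the statin arm: 158 × 0.90 = 142.2.
- Pooled rate: (23.7 + 22.9) / 300.2 = 0.1553, so the null standard error is 0.0419. The unpooled standard error is also 0.0419.
- Upper-tail rejection: 1 − Φ((1.645 × 0.0419 − 0.0111) / 0.0419) = 8.4%.

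The same method over a range (bias in points / upper-tail rejection, nominal 5%):

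| Withdrawn from statin arm | p_w = 0% | p_w = 5% | p_w = 10% | p_w = 15% |
|---|---|---|---|---|
| 3% (about 5 patients) | +0.46 / 6.3% | +0.31 / 5.8% | +0.15 / 5.4% | 0 / 5.0% |
| 5% (about 8) | +0.79 / 7.3% | +0.53 / 6.5% | +0.26 / 5.7% | 0 / 5.0% |
| 10% (about 16) | +1.67 / 10.6% | +1.11 / 8.4% | +0.56 / 6.6% | 0 / 5.0% |
| 15% (about 24) | +2.65 / 15.2% | +1.76 / 11.0% | +0.88 / 7.6% | 0 / 5.0% |

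The right-hand column is the case where withdrawal is unrelated to response: no bias, whatever the withdrawal rate.

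**4. What analysing as randomised costs in power**

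Suppose patients who stop the drug gain nothing from it. The expected statin pCR is then 0.25(1 − w) + 0.15w, and the difference falls from 10 points to 9.5 at w = 5% and 9.0 at w = 10%. With 158 per arm, power at two-sided 0.10 is 68% and 65%. At the one-sided 0.10 that reproduces 288, it is 80% and 77%.

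With no dilution, the null standard error is √(0.32/158) = 0.0450 and the alternative is √(0.315/158) = 0.0447. Power is Φ((0.10 − 1.645 × 0.0450) / 0.0447) = 72% two-sided and Φ((0.10 − 1.282 × 0.0450) / 0.0447) = 83% one-sided.

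**The case against.** The strongest reply is that section 2.3.9 never says withdrawn patients are left out of the pCR analysis. It says so of one other group, responders who are not operated on. Analysis populations are commonly set in a full protocol or analysis plan, and neither is shown. This stands: exclusion is an inference, and the claim that the randomised comparison is already broken goes further than the text.

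A reader might infer that frail or poorly tolerant patients leave the experimental arm alone while comparable controls stay in. The text does not support that. Three of the four triggers name no arm, and section 2.5 grades toxicity regardless of attribution, so a control can be withdrawn for chemoradiation toxicity. Only the study-drug trigger is exclusive to the statin arm; for the rest, the imbalance lies in detection.

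A reader might also infer that toxicity and survival data on these patients are lost. Sections 2.3.10 and 2.4 point the other way. But section 2.4 concerns survival only, applies only if phase III is run, and is hard to square with study withdrawal. What is established is a contradiction, not a loss.

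Finally, section 1.1 describes the drug as having very little toxicity, so drug-driven withdrawals may be few. That is fair, and it is why the range above starts at 3% and includes zero bias. None of this removes the rule itself, which is stated in two places, or the silence on collecting pathology afterwards.

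**Conclusion.** The point holds in limited form. As written, stopping the study drug or reducing it by more than one level removes a patient from the study, and only rosuvastatin patients can meet that condition. This permits loss after randomisation that depends on the arm, and it contradicts the commitment in section 2.4 to carry all phase II patients into the survival analysis.

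Any bias in pCR would most plausibly favour the statin. Its size cannot be derived from the documents. Over 3-15% withdrawn and 0-15% pCR among them, it runs from zero to about +2.6 points, with the upper-tail error between 5% and about 15%. Those figures assume no true effect, losses from the statin arm only and exclusion from the analysis; withdrawals among controls with similarly poor response would shrink the bias. They illustrate the exposure and do not predict it.

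This should be fixed, but it is not shown to be fatal. Confidence is moderate, because the analysis population is not in the text shown.

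**What to change.** - In section 2.3.9, define two separate events. Discontinuation of study drug keeps the existing drug-related triggers unchanged. Withdrawal from the study means only that the patient withdraws consent to follow-up.
- Remove non-compliance as a reason for study withdrawal. Record it as a protocol deviation instead.
- State that patients who stop the drug remain in the study, with surgery, pathology, adverse events, DFS and OS collected on the same schedule as everyone else.
- State that all randomised patients are analysed in their assigned arm, with a pCR rule for those without a specimen. Any per-protocol analysis is secondary.
- Reconcile sections 2.3.9 and 5 with sections 2.3.10 and 2.4.

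The cost is amendment wording. The protocol treats surgery, pathology and follow-up as standard care, so no extra visits or tests should be needed. The statistical cost is some dilution: on the assumption above, about 0.5 to 1 point of the expected 10-point difference if 5-10% of the statin arm stops the drug.
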